#### **Post treatment Visit (follow up at 6 and 12 months)**

- Treated patients will be seen at 6 and 12 months post-treatment visits, where they will perform self-HPV GeneXpert® test followed by VIA/VILI, Pap smear, Cervical Biopsy and ECC.
- Participants who will become pregnant during the study shall be counselled on risks excluded from the study and offered focalized antenatal and post-partum care.
- Data on women's quality of life and methods of contraception after screening procedures will be collected according to validated questionnaire;
- Participants treated by thermal ablation and an equivalent number of untreated patients (about 250 in each group) will be followed up by phone or interview for a survey on fertility outcomes. Participants from a previous study on cervical screening in Dschang, conducted by our study group, will be contacted as well for this follow-up study (about 50 in each group). Information about obstetrical outcomes may also be retrieved from medical records.

#### **Focus groups:**

- A semi-structured, pretested questionnaire will be used to explore the provider's perspective about possible barriers and facilitators to screening and second the user perspective discussing factors facilitating or limiting acceptability of self- sampling HPV.

**Qualitative interviews of community health workers (CHWs)** with the use of a semi-structured pretested questionnaire will be conducted to explore motivation and performance factors of CHWs and discuss recruitment strategies for cervical cancer screening.

### **6.1.3 Recruitment and screening**

The study site will be the health district of Dschang. The Dschang health district is a semi-rural area located in the West Region of Cameroon with an estimated population of 101,385 inhabitants. We evaluated that in the area under study 40,000 women are eligible for CC screening. Recruitment will be done through announcements made in women's associations, churches and integrated health centers (chief nurses of each center will be responsible for this recruitment); announcements will be broadcasted on local radios; and banners will be displayed in hospitals and other public places like markets to inform women of the screening campaign, specifying eligibility criteria, the period and the site of screening. Recruitment of women will also be done by community health workers (CHWs) in their respective "health area". CHWs will be recruited and trained by our study staff. A focus will be made on the free nature of this campaign.

During the screening campaign, the study will be explained to women (information sheet) and their participation will be requested. They will be asked to sign the consent form before the HPV-test. No compensation will be given to the study participants.

### **6.1.4 Medical chart:**

Study data will be collected on personalized electronic and paper medical chart. This will include socio-demographic and medical data (HPV results, cytology results (Pap smear), histologic results (biopsy and ECC), images and videos of the cervix (native, after application of acetic acid and lugol's iodine) and results at follow-up visits.

#### **6.1.5 Sample collection:**

Vaginal specimens for HPV test will be collected by participants themselves using flocked swabs after explanations by co-investigators. Two transport mediums will be used for those self-collected vaginal samples: NaCl 0.9%.

Cervical images will be obtained using a Smartphone (Samsung). The first image is that of the native cervix. The second part involves a 2-minute video of 1 frame/second (120 images) captured during application of a 5% acetic acid solution.-The third image is taken following application of Lugol's iodine.

Cervical biopsy will be guided by VIA/VILI if positive. It will be done at 6 o'clock in the transformation zone for participants with negative VIA/VILI. Biopsies will be performed by trained staff using Tischler forceps (Farla medical, United Kingdom).

Pap smear samples will be obtained with a spatula and transported in BD Surepath® vials (Becton Dickinson Company, Franklin Lakes New Jersey, USA) or ThinPrep (Hologic, Bedford, MA, USA). ECC will be done with an endobrush.

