| Measurements and Procedures: | 
Primary (Flow chart)
 
 
- After a community-based sensitization campaign, participants will undergo HPV-testing with GeneXpert® machines using self-collected samples (Flocked swabs) transported in a 0.9% sodium chloride (NaCl 0.9%) medium,
 
- HPV-negative women will be reassured and advised to do the next screening 5 years later,
 
- HPV-positive women will undergo the following sequence on the same day: VIA/VILI > Pap smear > Cervical Biopsy (VIA-guided biopsy for VIA-positive participants and random biopsy for VIA-negative participants) > Endocervical Curettage (ECC). All participants with a positive VIA/VILI will be treated with thermal ablation if eligible or Loop Electrosurgical Excision Procedure ((LEEP) for participants ineligible for thermal ablation).
 
- Specimens of Pap smear will be transported in BD SurePath™ vials (Becton Dickinson Company, Franklin Lakes New Jersey, USA) or ThinPrep™ (Hologic, Bedford, MA, USA) while those of biopsy, LEEP and ECC will be transported separately in formol (formaldehyde solution) vials.
 
- VIA/VILI will be interpreted on Smartphone images according to ABCD criteria and compared to VIA.
 
- Results of cytological and histological analysis will be disclosed to participants by midwives or obstetrician-gynecologist. Those requiring additional treatment will receive it for free.
 
- Follow-up visits will be organized 6 and 12 months later for women having received a treatment (self HPV GeneXpert® test > VIA/VILI > Pap smear > Guided biopsy + ECC).
 
 
Follow-up visits will be organized 12 months later for women having a positive screening test but VIA/VILI negative (self HPV GeneXpert® test > VIA/VILI > Pap smear > Guided biopsy + ECC)
 
Secondary
 
 
- Pictures of the cervix (native, after application of acetic acid (VIA) and lugol's iodine (VILI)) will be taken using a Smartphone (Samsung Galaxy™ S5). In addition to these 3 pictures, a 120 second long video of the cervix (120 images) will be recorded during the VIA. Then a database will be built-up.
 
- During the visit, participants will receive information on gynecological pathologies, including cervical cancer, sexually transmitted diseases and HIV, vaginal fistula
 
- All participants diagnosed with pre-cancer or cancer of the cervix will receive free of charge treatment
 
- Participants treated by thermal ablation and an equivalent number of untreated patients (about 250 in each group) will be followed up by phone or interview for a survey on fertility and obstetrical
 
 |

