#### First visit

- Information about the study and written informed consent
- Information about cervical cancer, STDs (including HIV) and fistula will be given to women;
- Socio-demographic data, acceptability of the self-test and data on women's quality of life will be collected according to validated questionnaire;
- HPV tests will be carried out on self-collected vaginal (flocked swabs transported in a 0.9% sodium chloride) medium samples using the GeneXpert machine. The results will be available after one hour.
- HPV-negative women will be reassured and advised to do the next screening 5 years later.
- HPV-positive women will undergo the following sequence on the same day: VIA/VILI > Pap smear

- > Cervical Biopsy (VIA-guided biopsy for VIA-positive participants and random biopsy for VIA-negative participants) > Endocervical Curettage (ECC). These tests will be done by the following experienced physicians.
- Pictures of the cervix during VIA/VILI (native image, video during acetic acid and image after lugol's iodine) will be stored on a digital device.
- VIA/VILI will be interpreted on smartphone pictures according to the ABCD criteria (relaxed IARC criteria).
- All participants with a positive VIA/VILI will be treated with thermal ablation if eligible or Loop Electrosurgical Excision Procedure (LEEP for participants ineligible to thermal ablation).
- Specimens of Pap smear will be transported in BD SurePath™ vials (Becton Dickinson Company, Franklin Lakes New Jersey, USA) while those of biopsy, LEEP and ECC will be transported separately in formol (formaldehyde solution) vials.
- Cytological and histological analyzes will be conducted both in Yaoundé and in Geneva.

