## **8.2 Assessments of primary endpoint/ outcome**

Sensitivity, specificity, positive predictive value and negative predictive value of VIA/VILI to detect CIN2+ lesions among HPV-positive women be calculated, using histology as gold standard.

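### How hard histology looks for CIN2+ depends on the VIA/VILI result, so sensitivity and NPV are biased upward if detection is poorer in VIA-negative women; no correction is planned

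*Protocol*

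**What the plan says.** Protocol 6.1.5 sets the sampling rule by index-test result. For positives, "Cervical biopsy will be guided by VIA/VILI if positive". For negatives, "It will be done at 6 o'clock in the transformation zone for participants with negative VIA/VILI". The first-visit procedures describe the same split as "VIA-guided biopsy for VIA-positive participants and random biopsy for VIA-negative participants". The Synopsis and the footnote to Figure 1 also call the second biopsy random, not 6 o'clock.

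All HPV-positive women also have endocervical curettage (ECC), for which 6.1.5 states "ECC will be done with an endobrush". Section 6.1.4 lists biopsy and ECC together as histological results.

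Section 8.2 then calls for accuracy measures of "VIA/VILI to detect CIN2+ lesions among HPV-positive women be calculated, using histology as gold standard", and 9.3.1 repeats this. Neither section separates the two kinds of histology. Section 6.1.9, on minimising bias, covers questionnaires, data checking and loss to follow-up only.

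Three further sources of information exist in VIA-negative women: a Pap smear, a recall of untreated women whose cytology or histology is abnormal (Figure 1 footnote), and a later visit: "Follow-up visits will be organized 12 months later for women having a positive screening test but VIA/VILI negative" (Synopsis). No section says that recall or 12-month findings change a woman's baseline disease status.

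**The concern.** Every HPV-positive woman is to have histology, so verification is complete, but it is not equally searching. A guided biopsy is aimed at the visible abnormality. A single biopsy at a fixed position in a woman with no visible abnormality can miss CIN2+ elsewhere on the ectocervix, and ECC samples the canal. Each such miss leaves the false-negative cell and enters the true-negative cell.

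The error therefore favours VIA triage on the primary endpoint, and it falls on the women whom triage would send home untreated. A larger sample does not remove it, and the 95% confidence interval does not reflect it.

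**Working it through.** **Inputs from the protocol (9.1).** 6000 women; 20% HPV-positive; 10% CIN2+ among these; 20% drop-out; expected sensitivity about 60% and specificity about 50%.

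**The plan's own figures.**
- 6000 × 0.20 = 1200; 1200 × 0.10 = 120 with CIN2+ and 1080 without.
- After drop-out: 120 × 0.80 = 96 and 1080 × 0.80 = 864.
- 1.96 × √(0.6 × 0.4 / 96) = 9.8 points; 1.96 × √(0.5 × 0.5 / 864) = 3.3 points.

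Both stated precisions reproduce. The problem is bias, not precision.

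**Assumptions not in the documents.** g is the probability that histology finds existing CIN2+ in a VIA-positive woman, and d is the same for a VIA-negative woman (non-guided biopsy plus ECC). I take 60% and 50% as the true sensitivity and specificity and 96 as the true number of cases.

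**Model.** Of 96 true cases, 57.6 are VIA-positive and 38.4 VIA-negative. Of 864 non-cases, 432 fall on each side.
- Observed TP = 57.6g; observed FN = 38.4d.
- Observed FP = 432 + 57.6(1 − g); observed TN = 432 + 38.4(1 − d).
- Reported sensitivity = 0.6g / (0.6g + 0.4d).

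| g | d | Sensitivity | Specificity | NPV |
|---|---|---|---|---|
| 1.0 | 1.0 | 60.0% | 50.0% | 91.8% |
| 1.0 | 0.9 | 62.5% | 50.2% | 92.7% |
| 1.0 | 0.7 | 68.2% | 50.7% | 94.3% |
| 1.0 | 0.5 | 75.0% | 51.1% | 95.9% |
| 0.8 | 0.8 | 60.0% | 49.8% | 93.5% |
| 0.8 | 0.6 | 66.7% | 50.2% | 95.1% |
| 0.8 | 0.5 | 70.6% | 50.4% | 95.9% |

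Sensitivity is unbiased when d = g. NPV is too high whenever d < 1, whatever g is. Specificity moves by about one point at most in these rows.

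**When the bias exceeds 9.8 points.** Set 0.6g / (0.6g + 0.4d) = 0.698.
- g = 1: d = (0.6/0.698 − 0.6)/0.4 ≈ 0.65.
- g = 0.8: d = (0.48/0.698 − 0.48)/0.4 ≈ 0.52.

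**Read in reverse.** With g = 1, an observed 60% implies a true value of 0.6 / (0.6 + 0.4/d): 51.2% at d = 0.7 and 42.9% at d = 0.5.

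**Check on an alternative reference.** Suppose 12-month CIN2+ in VIA-negative women were counted as baseline disease. Before drop-out there are 72 true positives, 120 true cases and 540 VIA-negative non-cases. If 2% of those 540 developed new CIN2+ within the year (assumed), 10.8 false negatives are added, and a true 60% becomes 72 / (120 + 10.8) = 55.0%, even if every baseline case was found.

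**The case against.** **ECC is part of the reference.** A reader might infer that ECC is collected but left out. Section 6.1.4 counts it as histology, and histology is the gold standard, so the natural reading includes it. LEEP tissue also goes to histology and nothing excludes it. This stands; ECC is inside d above.

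**The size is assumed.** A reader might infer that sensitivity will be overstated by more than the planned precision. The documents do not support this. They give neither d nor g; setting g = 1 is itself an assumption; and the expected 60% in 9.1 could already be a histology-observed value. If guided biopsy also misses disease the bias shrinks, and it disappears at d = g. The direction stands for d < g; the size does not.

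**The analysis plan may cover it.** Specimen definitions and sensitivity analyses are often left to an analysis plan, which is not at hand. But the protocol itself fixes both the index-dependent sampling and the direct comparison with histology, and its section on bias does not mention the difference.

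**Follow-up data are not a clean repair.** A reader might infer that 12-month histology should become part of the primary reference at no cost. It would apply to VIA-negative women only, so the reference would still depend on the index test, and new CIN2+ would bias sensitivity downward, as shown. Availability is also uncertain. The Synopsis lists guided biopsy and ECC among the 12-month procedures, while 6.1.6 says follow-up testing repeats the first visit, where only HPV-positive women were biopsied. Women still VIA-negative may have another 6 o'clock biopsy, and some will be lost. Nor does any section say that recall yields a new specimen. These objections stand, so this can only be a secondary analysis.

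**Conclusion.** The concern holds in direction. The plan makes the histological search depend on the test under evaluation, treats the results as one standard and states no correction, so sensitivity and NPV are biased upward whenever d < g. It would be unexpected for untargeted sampling to match guided sampling, but the protocol has no figure to settle this.

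The size is conditional. With a true sensitivity of 60%, the reported value is 62.5% to 75.0% for d from 0.9 to 0.5 at g = 1, and 70.6% at g = 0.8, d = 0.5. Specificity is little affected. At g = 1, d = 0.5, NPV reads 95.9% against a true 91.8%. That matters because section 4.1 cites reported sensitivities from 25% to 80%, and shifts of this order change where the trial falls in that range.

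**What to change.** In 8.2 and 9.3.1:

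1. State that the primary reference is baseline histology: biopsy, ECC and any LEEP specimen.
2. Prespecify a bias-corrected analysis, reported beside the primary estimate, over a stated range of d and g (for illustration, d from 0.5 to 0.9 and g from 0.8 to 1.0, with d no greater than g). Replace TP by TP/g and FN by FN/d, take the added cases out of FP and TN respectively, and recompute sensitivity, specificity and NPV.
3. Prespecify a secondary analysis that adds CIN2+ histology from recall and from the 12-month visit where obtained. State its limits: incident disease, loss to follow-up and repeat 6 o'clock sampling.

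Also reconcile the random biopsy of the Synopsis, the first-visit procedures and the Figure 1 footnote with the 6 o'clock biopsy of 6.1.5, and the 12-month biopsy wording of the Synopsis with 6.1.6. Which description is right is for the investigators to say.

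The cost is a little extra analysis and text, with no added procedure. The reported sensitivity will be accompanied by a less favourable range.

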#### **6.1.6 Follow-up:**

During follow up visit, tests will be done exactly as during the first visit.

#### **6.1.7 AVC development:**

A first version of the algorithm will be developed based on videos from VIA and histopathology results only, with a pixel-wise approach, i.e. each pixel will be independently classified. The classification is based on an artificial neural network (ANN) whose inputs and architecture will be optimized. Alternative approaches such as considering spatial or other clinical information will be investigated as well. As the project progresses, the number of data available will increase and the new data will be continuously used to retrain the system to achieve superior performances and generalization capability. Finally, the algorithm will be integrated into a smartphone app, allowing the user to obtain the result and the locations of the lesions immediately after recording the video.

#### **6.1.8 Laboratory analysis:**

Dry vaginal swabs will be placed and rinsed into tubes containing either 3 ml of NaCl 0.9% or 3ml PreservCyt® medium and the tubes will be vortexed for 15 seconds. Then 1 ml of each sample will be transferred to the cartridge and will be run on the GeneXpert machine. Once a valid result is obtained, the specimens will be discarded.

GeneXpert HPV analysis: The Xpert HPV analysis consists of real time PCR, using as internal assay control for specimen adequacy, the detection of a human reference gene (HMBS [hydroxymethylbilane synthase]) and an internal Probe Check Control (PCC). The PCC verifies reagent rehydration, PCR tube filling in the cartridge, probe integrity and dye stability.

This test includes reagents for the simultaneous detection of 14 hrHPV types (HPV16, 18, 31, 33, 35, 39, 45, 51, 52, 56, 58, 59, 66 and 68).

The assay utilizes multiple fluorescent channels for the detection of individual types of HPV, groups of HPV, and the human reference gene. Each fluorescent channel has its own cutoff parameters for target detection/validity. If sufficient signal is detected by the human reference gene, the assay results are reported as an overall "positive" if any type of targeted HPV is detected, but, additionally HPV16 and pooled HPV18/45 and, collectively, the other high-risk HPV types detected by the assay are reported specifically as "positive" or "negative."

#### **6.1.9 Methods of minimizing bias**

We will use validated pretests questionnaires to register the participants' data and a data manager will check all the database before analysis.

To reduce the number of loss to follow-up, the screen-and-treat strategy will hold in a single day and community agent will help looking for participants necessitating follow up.

## **7. PROJECT POPULATION**

The study setting we would like to implement would have the ability of screening 30 women (30 HPV tests) every day. According to our estimations, 6000 women could be screened during the recruitment period. Women will be recruited in the Dschang health district. (see chapter 4–6.1.3: recruitment and screening).

### **7.1 Criteria**

#### **7.1.1 Inclusion criteria**

- Women aged 30-49 years old and able to comply with protocol study
- Women understanding study procedures and accepting voluntarily to participate by signing an informed consent form (ICF).

#### **7.1.2 Exclusion criteria**

- Pregnancy
- Previous total hysterectomy
- Conditions that can interfere with visualization of the cervix

#### **7.1.3 Criteria for withdrawal / discontinuation of participants**

The participants can decide to withdraw from the study at any moment. We will explain to them that all medical and biological data obtained up until then will be used for the purposes of the study. In case of disease progression, patients will be managed according to the WHO guidelines for screening and treatment of precancerous lesions for cervical cancer prevention (Organization, 2013).

## 8. PROJECT ASSESSMENTS

### 8.1 Project flow chart/ table of procedures and assessments

[figure not shown]

Figure 1. Flow chart of the study

Use of GeneXpert® test; If suspicious of cancer refer to tertiary center;  All HPV positive women will have as quality control a cytology and guided biopsy (or random biopsy if VIA/VILI normal); a recall will be done if abnormal cytology/histology in untreated women. LEEP (Loop electrosurgical Excisional Procedure) in case of ineligibility to Thermal ablation. HPV: Human papillomavirus; LEEP: Loop electrosurgical excision procedure; VIA: Visual inspection with acetic acid; VILI: Visual inspection with Lugol's iodine

## **8.2 Assessments of primary endpoint/ outcome**

Sensitivity, specificity, positive predictive value and negative predictive value of VIA/VILI to detect CIN2+ lesions among HPV-positive women be calculated, using histology as gold standard.

## **8.3 Assessment of secondary endpoint/ outcomes**

In the conditions cited above, women with suspected precancerous lesions following VIA/VILI, will be immediately treated. The personnel will be trained to recognize fistulas. Patients with a fistula, will be transferred to the University Teaching Hospital of Yaoundé and will be treated free of charge. Voluntary women will be addressed to the HIV department for screening and free treatment. The feasibility of a prevention program for cervical cancer, sexually transmitted diseases and obstetrical fistula, will be assessed by the local teams in Cameroon and the University hospital of Geneva.

The University Hospital of Geneva will invest in the development of a consultation room in the district hospital of Dschang, with the purchase of a gynecologic table, a colposcope and initial renewable material. The GeneXpert® machine is already available in Dschang. Geneva will also insure the training of the medical team including nurses, one medical technician and CHWs, and the salary and/or financial compensations of this team during the 72-month study period. This team will then be supervised by a part-time gynecologist.

At the end, an activity report will allow us to evaluate the efficiency of the advertisement campaign, the number of screened women, and ability of the Ministry of Health to take over the fees of the material and human resources to carry on with the promotion of women health.

## **8.4 Assessment of other study variables**

Socio-demographics and past obstetric and gynecological history will be assessed during collection at the first screening visit.

At the end, the extrapolation of our data, will give us an idea of the prevalence of HPV infection and cervical pre-cancer and cancer among Cameroonian women.

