| Objective(s): | 
Primary objective
 
 
- To determine the sensitivity and specificity HPV test followed by VIA/VILI to detect cervical precancerous lesions in a screen-and- treat strategy using histology as gold standard
 
 
Secondary objectives:
 
 
- To create a database of cervical images for continuous clinical education and research,
 
- To assess the impact of HPV-positive screening on the level the women's quality of life among women in Cameroon,
 
- To examine the impact of the screening on sexual and reproductive health among women with HPV,
 
- To assess the impact of HPV-positive screening on the level of anxiety among women,
 
- To better understand the accessibility of HPV-self sampling and potential barriers to screening,
 
- To inform women and their families about gynecological pathologies, including cervical cancer, sexually transmitted diseases (including HIV) and vaginal fistula,
 
- To assess women acceptability of self-HPV, thermal ablation and screening process,
 
- To study the HPV infection positivity and HPV clearance, as well as the prevalence of cervical cancer and pre-cancer in our population,
 
- To assess thermal ablation efficacy for the treatment of precancerous lesions,
 
- To offer the possibility to perform HIV test in HIV center in Dschang,
 
- To expand coverage rate and improve access to cervical cancer screening programs with participation of community health workers.
 
- To develop a detection algorithm using cervical images that can identify cervical precancerous lesion
 
- To assess the impact of thermal ablation on fertility and obstetrical outcomes
 
- To develop an Automated VIA Classifier (AVC) that can help identify cervical precancerous lesions based on a 2-minute video of the cervix during VIA and machine learning
 
- To assess women's, the community's and healthcare providers' acceptability of the AVC test
 
- To assess the AVC test performance
 
 |

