### 5.2.2 Secondary endpoint/outcomes

- Provide teaching material for professional training on cervical cancer prevention through VIA/VILI (cervical images database)
- Sexual dysfunction score, score of anxiety and method of contraception after screening procedures
- Willingness to participate in the 3T screening program;
- Prevalence of HPV, cervical pre-cancer and cancer among Cameroonian women
- HPV clearance at 6 and 12 months follow up
- Prevalence of CIN2+ disease at the 12-month follow-up
- Acceptability of self-HPV test, thermal ablation and cervical cancer screening procedures
- Women's experiences and attitudes on cervical cancer screening
- Proportion of side effects and complications after thermal ablation or LEEP
- VIA test-positive rate (HPV-positive women);
- VIA test-positive rate after 1- year follow-up of VIA-negative tests
- Thermal ablation efficacy
- Increase awareness on gynecological pathologies, including cervical cancer, sexually transmitted diseases and HIV, vaginal fistula in the community of the study area
- Number of women screened with and without the participation of community health care workers.
- Specificity and sensitivity of the AVC test, using histology as the reference standard
- Acceptability of the AVC test

The demand for programs to control CC in low-resource settings is strong. Lessons that we have learned from our previous experience, combined with results of recent researches have put our group in an excellent position to identify innovative and cost-effective strategies for reducing CC morbidity and mortality in developing countries. The obtained data will determine the level of support, which will be needed to maintain high-quality CC prevention services in equipment and provider skills. We expect also that our data will also determine how a CC- screening program might be established in a sustainable prevention strategy.

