#### 6.1.2 Study design

Single-center prospective and longitudinal (cohort) study

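### Secondary outcome: prevalence is stated for Cameroonian women, but the design supports only women aged 30-49 attending screening in one district, and the pre-cancer and cancer figure is a lower bound even for them

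*Protocol*

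**What the plan says.** The target population of the prevalence outcome differs from place to place in the protocol.

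- Section 5.2.2 lists as a secondary outcome "Prevalence of HPV, cervical pre-cancer and cancer among Cameroonian women". The French synopsis outcome likewise names the Cameroonian woman.
- Section 8.4 gives the route: extrapolation of the study data "will give us an idea of the prevalence of HPV infection and cervical pre-cancer and cancer among Cameroonian women".
- The English synopsis objective is narrower: "the prevalence of cervical cancer and pre-cancer in our population". The French synopsis objective also refers to the study population.
- The English synopsis outcome and the objective in section 5.1.2 name no population for prevalence.

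The design is described in section 6.1.2 as "Single-center prospective and longitudinal (cohort) study". On the setting, section 6.1.3 says: "The Dschang health district is a semi-rural area located in the West Region of Cameroon with an estimated population of 101,385 inhabitants". On recruitment it says: "Recruitment will be done through announcements made in women's associations, churches and integrated health centers". It adds local radio, banners and recruitment by trained community health workers, for a campaign promoted as free. Eligibility in section 7.1.1 is "Women aged 30-49 years old and able to comply with protocol study".

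Under section 6.1.2, first visit, HPV-negative women receive no further examination and are advised to return for screening in five years. VIA/VILI, Pap smear, biopsy and endocervical curettage are done only in HPV-positive women.

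**The concern.** An outcome should name the population that the data can describe. Here the outcome list and section 8.4 name all Cameroonian women, without limit of age or area, while the synopsis objectives name the study population. The two cannot both be the target, and the design fits only the narrower one.

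There are two separate problems:

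- **Selection** affects HPV prevalence and disease prevalence alike. Women who come to a free campaign in one district may differ from those who do not, from women elsewhere in the country, and from women outside ages 30-49.
- **Verification** affects only pre-cancer and cancer. Disease in HPV-negative women cannot be found under this plan and is in effect counted as absent.

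The results are to be reported to the Cameroonian health authorities (section 11.1). A figure labelled national could be taken as a planning figure for the country.

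**Working it through.** **1. The protocol's own counts (section 9.1).** 6,000 × 0.20 = 1,200 HPV-positive women; 1,200 × 0.10 = 120 with CIN2+; 1,200 − 120 = 1,080 without. After 20% drop-out, 96 and 864 remain. With half-width = 1.96 × √(p(1−p)/n):

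- sensitivity: 1.96 × √(0.6 × 0.4/96) = 9.8 points
- specificity: 1.96 × √(0.5 × 0.5/864) = 3.3 points

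Both stated precisions reproduce. They concern VIA accuracy in HPV-positive women. The protocol states no precision for any prevalence.

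**2. Target against design.**

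| Element | Outcome (5.2.2, 8.4, French synopsis) | Design |
|---|---|---|
| Area | Cameroon | One semi-rural health district |
| Age | No limit | 30-49 |
| Selection | Not addressed | Voluntary attendance after announcements or contact by community health workers; no sampling frame |
| Disease ascertainment | Not addressed | Histology in HPV-positive women only |

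Section 11.3 mentions two district hospitals, against the single centre of section 6.1.2. Neither reading gives a national sample.

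**3. Verification gap (pre-cancer and cancer only).** HPV-negative women: 6,000 − 1,200 = 4,800, or 80% of the cohort, with no histology.

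Detected CIN2+ prevalence, before any drop-out: 120/6,000 = 2.0%. Sampling half-width: 1.96 × √(0.02 × 0.98/6,000) = 0.35 points.

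Let r be the CIN2+ risk in HPV-negative women. The documents do not give it, so the range is an assumption. Prevalence among attenders = (120 + 4,800 × r)/6,000:

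- r = 0: 2.0%
- r = 0.1%: (120 + 4.8)/6,000 = 2.08%
- r = 0.5%: (120 + 24)/6,000 = 2.4%

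The shift is 0.08 to 0.4 points, upward only. At the top of the range it is about the size of the sampling half-width.

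**4. Selection (illustration for HPV prevalence).** Sampling half-width: 1.96 × √(0.2 × 0.8/6,000) = 1.0 point, so sampling error is small. The documents give no size for selection bias. Suppose, purely as an assumption, that attenders' HPV prevalence is 0.8 to 1.25 times that of non-attenders. With 20% in attenders, non-attenders would have 20/0.8 = 25% or 20/1.25 = 16%. The protocol gives two bases for the share attending:

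- 25,000 women aged 30-49 (section 4.2): 6,000/25,000 = 24%. District prevalence is 0.24 × 20 + 0.76 × 16 = 17.0% to 0.24 × 20 + 0.76 × 25 = 23.8%.
- 40,000 women eligible for screening (section 6.1.3): 6,000/40,000 = 15%. District prevalence is 0.15 × 20 + 0.85 × 16 = 16.6% to 0.15 × 20 + 0.85 × 25 = 24.3%.

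This reaches only as far as the district. Nothing in the documents allows the further step to the country or to other ages to be quantified.

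**The case against.** The strongest reply is that section 8.4 is a hedged remark under other study variables. It promises an idea of prevalence, not an estimate. There is no national estimator, no precision target and no hypothesis, and the study is sized only for VIA accuracy. The synopsis objectives already give the narrower target, so the protocol can be read charitably as meaning its own population.

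Much of this stands. A reader might infer that the trial will publish a national prevalence with an interval far too narrow for the population named. The documents do not support that: they specify no interval for prevalence, and the 95% intervals in the synopsis belong to sensitivity, specificity and predictive values. Nor can the size of selection bias be read from the documents; the ranges above rest on an assumed ratio.

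A reader might also infer that the missing biopsies distort HPV prevalence. They do not, because every attender is tested for HPV. And calling the sample purely self-selected responders to announcements would be incomplete, since community health workers also recruit. Attendance nevertheless remains voluntary and unsampled.

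What the reply does not meet is section 5.2.2. That is the formal outcome list, it names Cameroonian women, and it carries no hedge. An analysis plan could add detail, but it could not supply a sampling frame or verify HPV-negative women after the fact.

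**Conclusion.** The point holds as an inconsistency in the target population together with a claim wider than the design. Sections 5.2.2 and 8.4 and the French synopsis outcome point to the nation; the synopsis objectives, English and French, point to the study population. Only the latter is attainable.

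For pre-cancer and cancer, the figure is a lower bound even among attenders: 2.0% on the protocol's assumptions, against 2.1-2.4% if 0.1-0.5% of HPV-negative women have CIN2+. This takes histology as correct and rests on an assumed risk in HPV-negative women. The understatement is modest. The main defect is the population named.

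This is a minor correction to one secondary outcome. The analysis of VIA/VILI accuracy among HPV-positive women (section 8.2) and the sample size are unaffected.

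**What to change.** - In section 5.2.2 and the French synopsis outcome, replace the national target with: *among women aged 30-49 attending screening in the Dschang health district*. This agrees with the synopsis objectives in both languages.
- In section 8.4, delete the extrapolation sentence; if a statement on prevalence is kept there, use the same population wording.
- Wherever pre-cancer and cancer prevalence is named, label it as detected through HPV-positive women, a lower bound. HPV prevalence needs no such label.

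Age standardisation to the district is not requested. The documents give no age distribution within 30-49, and standardising for age would not correct for who chooses to attend.

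The cost is wording only: no new data, visits or participants. The price is a narrower claim.
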